### Intervention

#### OSI

Parents work through a series of seven online modules which include simple text, audio versions of text, videos and animations, interactive activities, and inbuilt questionnaire measures. Online modules are released weekly for parents to complete in their own time. Each module takes about 20–30 min to complete and is supported by a brief telephone session with a CWP (approximately 20 min) once a week for 7 weeks, and a follow-up telephone session 4 weeks later. Modules teach parents cognitive behavioural strategies to apply in their child’s day-to-day life, including how to explore their child’s anxious thoughts, testing these thoughts by facing fears and problem-solving challenges, and the telephone sessions are designed to review progress and support parents to practise the strategies and problem solve any challenges. There is also an accompanying, optional game for mobile devices that is designed to help motivate the child to face their fears. We anticipate that one or two CWPs will support OSI delivery in this study. CWPs have received post-graduate training in the delivery of low-intensity psychological therapies for children and adolescents who experience difficulties with anxiety, low mood and behavioural problems. Study CWPs will receive regular supervision from clinical psychologists with expertise in treating childhood anxiety disorders.

### Outcomes

#### Feasibility outcomes and criteria for progressing to cluster randomised controlled trial

Feasibility outcomes related to negative impacts, acceptability, recruitment, and retention rates, and proposed clinical and health economic outcome measures, together with associated progression criteria are detailed in Table 1. To facilitate rapid progression to the main trial once the feasibility study is complete, interim criteria for progressing to the set-up phase for the cluster randomised controlled trial will be assessed once participant recruitment is complete, but while data collection is still ongoing. Once all data collection and required analyses are complete, the Study Steering Committee will then assess the full criteria for progressing to recruitment for the main trial. If there are no serious negative impacts or serious concerns about the acceptability of the procedures, at least 80% of the target population complete all assessments, and at least 12% of parents of children in study classes participate in OSI, we plan to progress to the randomised controlled trial and implement any indicated changes to the study procedures and outcome measures. If there are any serious harms or serious concerns about the acceptability of the study procedures, we will consult the Study Steering Committee about not progressing to the main trial. If the recruitment and retention rates are slightly below our targets (70–79% of the target population complete all assessments, and/or 9–11% of parents of children in study classes participate in OSI), we will consult the Study Steering Committee about progressing and consider whether changes to the protocol may improve recruitment/retention, and if recruitment/retention rates are markedly below our targets (< 70% of target population complete all assessments and/or < 9% of parents of children in study classes participate in OSI), we will consult the Study Steering Committee about not progressing to the main trial. However, as data collection is planned during the context of the COVID-19 pandemic, and associated restrictions (e.g. school closures, researchers unable to visit schools) may have an impact on recruitment/retention, the Study Steering Committee will consider this context when assessing the progression criteria related to recruitment and retention rates to determine whether continuing to the main trial is recommended or not.

**Table 1 Tab1:** Feasibility outcomes and criteria for progressing to cluster randomised controlled trial

Feasibility outcome	Measure/method of assessment	Interim criteria for progressing to cluster randomised controlled trial set-up	Criteria for progressing to recruitment for cluster randomised controlled trial	Potential recommendations for cluster randomised controlled trial protocol
Negative impacts of the study procedures	• Monitoring participant reports throughout • Bespoke acceptability questionnaire (child-, parent-, teacher-report) • Qualitative interviews/discussion groups (children, parents/carers and school staff) • Study Steering Committee judgement	GO: Serious negative impacts have not arisen at this stage as a result of participation in the study procedures	GO: Serious negative impacts have not arisen as a result of participation in the study procedures	• Implement indicated changes to study procedures to minimise the risk of any negative impacts
		STOP: There are serious concerns about harms of study procedures, confirmed by Study Steering Committee	STOP: There are serious concerns about harms of study procedures, confirmed by Study Steering Committee	
Acceptability of all study procedures, including screening, feedback for parents/carers, brief intervention	• Monitoring participant reports throughout • Bespoke acceptability questionnaire (child-, parent-, teacher-report) • Qualitative interviews/discussion groups (children, parents/carers and school staff) • Study Steering Committee judgement	GO: No serious concerns have arisen about the acceptability of the study procedures	GO: No serious concerns about the acceptability of the study procedures	• Implement indicated changes to study procedures to minimise any concerns and maximise acceptability among children, parents/carers and school staff
		STOP: There are serious concerns about the acceptability of study procedures, confirmed by Study Steering Committee	STOP: There are serious concerns about the acceptability of study procedures, confirmed by Study Steering Committee	
Recruitment and retention rates	• Number (%) of eligible participants who complete baseline and follow-up assessments • Number (%) of participants who screen positive (target population) who complete baseline and follow-up assessments • Number (%) of participants who participate in OSI	GO: • At least 80% of participants who screen positive (target population) complete the baseline assessment. • At least 12% of parents of children in study classes^a^ to date participate in OSI	GO: • At least 80% of participants who screen positive (target population) complete all assessments. • At least 12% of parents of children in study classes^a^ participate in OSI	• Implement indicated changes to study procedures to improve recruitment/retention rates
		AMEND: • ≥ 70% and < 80% of participants who screen positive (target population) complete the baseline assessment. • ≥ 9% and < 12% of parents of children in study classes^a^ to date participate in OSI	AMEND: • ≥ 70% and < 80% of participants who screen positive (target population) complete all assessments. • ≥ 9% and < 12% of parents of children in study classes^a^ participate in OSI	
		STOP: • < 70% of participants who screen positive (target population) complete the baseline assessment. • < 9% of parents of children in study classes^a^ to date participate in OSI	STOP: • < 70% of participants who screen positive (target population) complete all assessments. • < 9% of parents of children in study classes^a^ participate in OSI	
Relevance and acceptability of all clinical and health economic outcome measures	• Proportion of missing data and patterns in missing responses/measures at baseline and follow-up assessments • Descriptive statistics for clinical and health economic outcomes • Qualitative interviews/discussion groups (children, parents/carers and school staff)			• Implement indicated changes to proposed outcome measures

*GO* = progress to cluster randomised controlled trial. *AMEND* = Consult Study Steering Committee regarding progression. *STOP* = Consult Study Steering Committee regarding not progressing

^a^Based on estimated 60% participation in parent-report screening; 20% screen positive

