### Sample size

We aim to recruit approximately 360 children from 6 primary/junior schools (30 children per class, two classes per school), and their parents and class teachers. This sample size will allow us to assess feasibility outcomes in schools with varied geographic and demographic profiles, and will provide a sufficient number of families with varied characteristics to identify any issues with acceptability or feasibility. In line with a recent primary school-based trial in the UK [19], we expect to collect parent baseline measures from approximately 60% of children in participating classes (*n* = 216), and on the basis of findings in our measurement development study [17], we expect approximately 20% of these will screen positive (target population: *n* = 43).

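### The 12% OSI progression bar equals the expected screen-positive share with no uptake term, so unless other families join, GO corresponds to 100% acceptance and STOP starts below 75%

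*Protocol article*

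**What the plan says.** The section on feasibility outcomes and progression criteria makes it one condition for progressing that "at least 12% of parents of children in study classes participate in OSI". Table 1 repeats this, with AMEND at "≥ 9% and < 12% of parents of children in study classes" and STOP at "< 9% of parents of children in study classes participate in OSI". The same limits apply at the interim review, counted on participation to date. Footnote a gives the only stated basis: "Based on estimated 60% participation in parent-report screening; 20% screen positive".

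The Sample size section uses the same two rates to obtain the target population. It starts from about 360 children, then says "we expect to collect parent baseline measures from approximately 60% of children in participating classes" (n = 216), and then "we expect approximately 20% of these will screen positive" (n = 43).

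Three other parts of the article bear on the point:

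- **Entry to OSI.** Under Procedures, a screen-positive family is contacted, has a feedback call and is invited to OSI, and starts only if the parent agrees.
- **Open access.** Background, Design and Procedures make OSI available to any interested family in the participating classes, whatever the screening result.
- **Meaning of the bands.** The Table 1 legend defines AMEND and STOP as consultations with the Study Steering Committee.

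**The concern.** The footnote derives one quantity and the criterion applies the result to another. The product of the two rates is the expected proportion of children who screen positive. The criterion concerns the proportion of parents who go on to take part in a parent-led course of seven weekly modules with telephone support. Arranging the call, the invitation and the parent's agreement lie between the two, and no acceptance rate covers that step.

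This is one of only two numerical progression criteria. The other, in the same row of Table 1, allows up to 20% of the target population to miss assessments before GO is lost. The OSI bar allows no loss from the group on which it is based. If screening goes exactly as planned and acceptance is good but incomplete, the result falls into AMEND or STOP unless families outside the target population make up the difference. Because their contribution is not planned, the committee would have no stated expectation against which to read a figure above or below 12%.

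**Working it through.** **Inputs.** From Sample size: 6 schools × 2 classes × 30 children = 360; 60% screened; 20% of those positive. From Table 1: GO ≥ 12%, AMEND ≥ 9% and < 12%, STOP < 9%. The article gives neither acceptance among screen-positive families (*u*) nor uptake among all other families (*v*). Both are varied below as assumptions.

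**Step 1: reproduce the plan's figures.** 0.60 × 360 = 216. 0.20 × 216 = 43.2, stated as 43. 43.2/360 = 0.60 × 0.20 = 12.0%, exactly the GO bar.

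**Step 2: acceptance implied with no other entrants.** Expected participation is 0.12 × *u*.

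- GO: 0.12/0.12 = 100%.
- Lower edge of AMEND: 0.09/0.12 = 75%, with STOP below it.
- Expected participation is 10.8% at *u* = 90%, 9.6% at 80%, 8.4% at 70% and 7.2% at 60%.

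**Step 3: whole numbers.** 12% of 360 is 43.2, so a strict reading needs 44 families for GO. 9% of 360 is 32.4, so 33 families is AMEND and 32 is STOP. Of 43 positives, 33 is 76.7% and 32 is 74.4%.

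**Step 4: other entrants needed.** Outside the target population there are 360 − 43 = 317 families.

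- At 75% acceptance (about 32 of 43), GO needs 44 − 32 = 12 others, or 12/317 = 3.8%.
- At 60% acceptance (about 26 of 43), GO needs 44 − 26 = 18 others, or 18/317 = 5.7%.
- A total of 44 can therefore be 43 + 1 or 26 + 18, and the criterion does not distinguish them.

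**Step 5: classification probabilities.** The count is taken as Binomial(360, 0.12*u* + 0.88*v*), with GO at 44 or more and STOP at 32 or fewer.

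| Acceptance *u* | Other uptake *v* | P(GO) | P(STOP) |
|---|---|---|---|
| 100% | 0 | 0.47 | 0.04 |
| 90% | 0 | 0.21 | 0.14 |
| 80% | 0 | 0.06 | 0.36 |
| 80% | 2% | 0.33 | 0.08 |
| 80% | 3% | 0.53 | 0.03 |
| 80% | 4% | 0.72 | 0.01 |
| 70% | 0 | 0.01 | 0.67 |
| 60% | 0 | below 0.001 | 0.91 |
| 60% | 2% | 0.02 | 0.53 |
| 60% | 4% | 0.20 | 0.15 |

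The model treats families as independent, although they are grouped in 12 classes.

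**Step 6: sensitivity to the planning rates, no other entrants.** Required acceptance is the limit divided by (screened × positive).

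| Screened | Positive | GO needs | STOP below |
|---|---|---|---|
| 60% | 20% | 100% | 75% |
| 60% | 25% | 80% | 60% |
| 70% | 20% | 86% | 64% |
| 50% | 20% | 120% (unreachable) | 90% |

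**The case against.** A reader might infer that the protocol assumes every screen-positive family accepts OSI and that the study stops if fewer than 75% do. The document does not support that reading, for these reasons:

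- **The numerator is wider.** The criterion counts any parent of a child in the study classes. Open access is deliberate, because the screen will miss some children who could benefit, and every feedback letter describes OSI. The 100% and 75% figures hold only if nobody else joins and the 60% and 20% rates are met. Step 5 shows how far modest self-referral changes the picture at 80% acceptance. This stands, and the point is worded conditionally for that reason.
- **STOP is a consultation.** The committee is asked about not progressing, and it will also weigh the COVID-19 context. This stands too, and it lowers the severity. It does not supply the missing term: the committee still reads the result against these bands, and the COVID-19 allowance concerns disruption, not ordinary refusal.
- **44 against 43 is rounding.** The 360, 60% and 20% are all approximate, and a bar placed at its expected value is met only about half the time in any case. Agreed; nothing here rests on that one-family gap.
- **Ambition is the sponsor's choice.** A demanding bar is legitimate, and the document cannot show that 12% is the wrong number. The fault is that its printed rationale derives a different quantity.
- **Uptake will be reported separately.** The Statistical analysis section plans OSI uptake for the target population and for all children in the classes, so the mix will be visible. The progression rule still sets no expectation for either part.

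**Conclusion.** The point holds in conditional form and should be fixed, although it is not critical. The 12% GO bar is the expected screen-positive share carried over unchanged to OSI participation. If 60% are screened, 20% of those are positive and no other family joins, GO corresponds to 100% acceptance and the STOP band begins below 75%. At 80% acceptance under those conditions, P(GO) is about 0.06 and P(STOP) about 0.36. If 2% to 4% of other families join (assumed rates), P(GO) rises to between 0.33 and 0.72. How the study is classified thus depends heavily on two quantities that the article does not state: acceptance in the target population and uptake outside it. The consequence is a progression signal that is hard to interpret. It is not an automatic termination, and it biases no treatment effect, since this is a single-arm feasibility study.

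**What to change.** Before uptake data are seen, re-derive the GO, AMEND and STOP limits for OSI in Table 1 (interim and final columns) and in the accompanying text. Each limit should be 60% × 20% × the acceptance rate required at that level for the main trial, plus any share of all parents planned to come from families outside the target population. State both figures in footnote a. If families outside the target population are not meant to count towards the bar, say so and restrict the numerator.

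The acceptance rate is for the sponsor to set; the article gives no value from which to choose one. As an illustration of the arithmetic only, 80% acceptance with no planned share from others would give 0.60 × 0.20 × 0.80 = 9.6%.

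The cost is one footnote, the two cut-off percentages in Table 1 and the matching sentences in the text. The downside is that the GO percentage will probably become lower, which could look like a relaxed standard if the change were made after uptake is known.

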#### Child clinical outcome measures

##### Brief child anxiety screen

A 2-item parent-report questionnaire will be used to assess whether the child is experiencing problems with anxiety, and to identify the target population. The items assess the extent to which a child’s fears, worries or anxiety cause distress (Do your child’s fears, worries or anxiety upset or distress your child?) and interfere with family life (Do your child's fears, worries or anxiety make things difficult for your family as a whole?). Parents rate each item on a 4-point scale (No, not at all = 0; yes, only a little = 1, yes, quite a lot = 2; yes, a great deal = 3), and responses are summed to produce a total score. A cut-off score of ≥ 3 identifies children with anxiety disorders with 76% sensitivity and 80% specificity [17]. Children who score ≥ 3 out of 6 at baseline will be the target population, and total scores and screening outcomes (screen positive = score 3–6; screen negative = score 0–2) will be calculated at baseline and follow-up.

##### Child anxiety symptoms and interference

Child-, parent-, and teacher-report versions of the Brief Spence Children’s Anxiety Scale (SCAS-8-C/P/T) [20] and the child- and parent-report versions of the Revised Children’s Anxiety and Depression (RCADS)-Anxiety Scale will be used to assess anxiety disorder symptoms. The SCAS-8-C/P/T each consist of 8 items from the original SCAS [21, 22], and items are rated on a 4-point scale (0–3) that are summed to provide a total score. The SCAS-8 has the advantage of brevity, with evidence to support its ability to discriminate between children (aged 7–11) with anxiety disorders from a community sample [20]. The RCADS-C/P [23, 24] is widely used in clinical and community settings, and anxiety total scores reflect the sum of 37 anxiety items, each rated on a 4-point scale (0–3). Including these two alternative child anxiety symptom measures will provide the opportunity to assess the relevance and acceptability of both and inform our decision on whether to include one or both in the main trial. However, as neither the SCAS-8 nor the RCADS captures information about interference related to a child’s anxiety, we will also include additional items to assess anxiety-related interference for each reporter. Alongside the SCAS-8, parents will complete the 2-item brief anxiety screen detailed above, and children and teachers will complete the following corresponding items: children: Do fears or worries upset you?; Do fears or worries stop you from doing things?; Do your fears or worries make things difficult for people around you (e.g. family, friends, teachers)?; teachers: Do fears, worries or anxiety upset or distress this child?; Do this child's fears, worries or anxiety make things difficult for you or the class as a whole? Responses to these child- and teacher-report interference items will be summed to provide respective total scores (child: range 0–9; teacher: range 0–6).

##### Broader child clinical outcomes

Child low mood symptoms will be assessed using the child- and parent-report 10-item RCADS-Depression Scale (4-point rating scale (0–3); total score range 0–30). The well-established child- and parent-report Strengths and Difficulties Questionnaire (SDQ-C/P) [25, 26] will be used to measure broader emotional and behavioural symptoms, providing a Total Difficulties score (range 0–40), as well as subscales scores (emotional problems [range 0–10]; Conduct problems [range 0–10]; Peer problems scale [range 0-10]; Hyperactivity [range 0–10]).

#### Health economic outcomes and measures

##### Quality of life

Child- and parent-report versions of the Child Health Utility-9D (CHU-9D) [27, 28] and the EQ-5D-Y [29] will be used to assess children’s quality of life. The CHU-9D is a preference-based measure of health-related quality of life which allows the calculation of Quality Adjusted Life Years (QALYs) for use in cost utility analysis. It includes nine dimensions (worried, sad, pain, tired, annoyed, schoolwork, sleep, daily routine, activities) each with five ordered response levels. The measure was originally developed and validated with children aged 7–11 years. The EQ-5D-Y is a child-friendly version of the EQ-5D that was introduced by the EuroQol Group in 2009 as a comprehensible instrument suitable for measuring health-related quality of life of children and adolescents aged 8–15 years. It includes five dimensions (mobility; looking after myself; doing usual activities; having pain or discomfort; and feeling worried, sad or unhappy) each with three ordered response levels. It can be used to derive QALYs. There is no clear standard when it comes to measuring Health-related Quality of Life Instruments for children and young people, but the CHU-9D and the EQ-5D-Y are among the most used instruments. We will therefore use both in this study to inform our choice for the main trial.

To measure parents’ quality of life, we will use the EQ-ED-5L [30]. The EQ-5D-5L is a well-validated preference-based measure of health-related quality of life in adult populations, designed to estimate quality adjusted life years (QALYs) and widely used across disease areas. It includes five dimensions covering domains of everyday life, i.e., mobility, self-care, usual activities, pain/discomfort, and anxiety/depression, each with five ordered levels of response.

##### Resource use

A societal perspective for resource use will be adopted in recognition of the fact that economic costs of mental health have wide consequences beyond the health and social care sectors, including education and the labour market. We will use a modified version of the Client Service Receipt Inventory (CSRI) [31] form and therapist, supervisor and school staff logs to identify and measure: (i) resources used in delivering the iCATS-i2i screening, feedback, and intervention procedures; (ii) child and parent individual resource use data including health and social care system and other sector resources (e.g. GP use, referrals, child and adolescents mental health services, educational services); (iii) other child-, family-, society-borne resource use, including child time off school, parent time spent related to child anxiety problems, including time off work (i.e. productivity losses for the wider economy). Parents will complete the modified CSRI at baseline (with reference to the previous 3 months) and follow-up (with reference to the study period). At baseline, parents will also be provided with a diary to keep a record of service use and time off work/school, to facilitate answering the questions at follow-up. School staff will be asked to complete a log throughout the study to record time spent on study activities (e.g. administering questionnaires, distributing information to families), and study therapists and supervisors will complete logs to record time spent on activities related to delivering OSI.

